## Methods

### Clinical neurological and cognitive evaluation

Healthy relatives of CJD patients will undergo the following longitudinal assessments:

Collection of clinical data, including cognitive, behavioral, and autonomic function.Collection of Blood, urine, and CSF biomarkers.Electrophysiological measurements and assessment of other sleep characteristics.structural and functional markers on brain MRI.Gait and movement assessments.

Data regarding demographics, medical and family history as well as physical and neurological examinations will be collected on all participants. Participants will be asked to provide information as to food and drink consumption on the day of the exam. Concomitant medications, including over-the-counter dietary supplements (e.g., herbal remedies), or prescription medications, will be recorded. Evaluation of individuals who take antibiotics will be deferred until their course of antibiotics ends, with a washout period of at least 1 week.

The justification for the need for LP in this study is based on several factors. Firstly, CJD is a rapidly progressive disease, and early detection is critical for improving patient outcomes. The yearly analysis of the CSF may help identify prodromal changes in brain biomarkers, particularly the aggregation of PrP^sc^, which may indicate onset of disease before appearance of clinical symptoms. Secondly, the protocol has been granted approval by the ethics committee, taking into account the exceptionally high penetrance of the mutation and the valuable data that can only be obtained from CSF. This taken together with the fact that the LP procedure is considered safe led the committee to decide that its potential benefit outweighs the risk. Thirdly, participants who are not willing to repeat the LP procedure are not excluded from the study. However, in the event that they exhibit symptoms suggestive of conversion into the disease, an LP is carried out as part of the clinical diagnostic process. This ensures that participants are given the option to opt-out of the LP procedure while still receiving the necessary medical attention should they develop symptoms. In conclusion, there is a need for lumbar puncture in healthy carriers of the E200K mutation for CJD as part of a clinical trial studying the natural history of the disease and the prodromal phase. CSF sampling in a high risk healthy population is critical in order to identify markers associated with the prodromal phase of the disease and therefore was approved by the ethics committee. Participants who do not wish to undergo LP are not excluded and are able to participate in the study.

All gCJD patients will be scored according to the National Prion Monitoring Cohort (NPMC) Scale (MRC Prion Disease Rating Scale) [36], which is a multimodal scale assessing both cognitive impairment and daily function disability. This scale consists of 11 parameters: bowel function, bladder function, toilet use, bathing, feeding, transfer and mobility, stairs, best verbal response, memory and orientation to surroundings, judgment and problem-solving, and use of tools. Each section is scored between 0 and 4 with 0 indicating complete disability and 4 normal ability, for a maximum of 20 points.

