### Study population

Inclusion/ exclusion criteria.

gCJD patients’ inclusion criteria:

Diagnosis of CJD at baseline/ screening.Age 18 years or older at baseline.Confirmation of E200K mutation or willingness to undergo genetic testing as part of the pre-screening for new patients.Ability to provide written informed consent under Good Clinical Practice (GCP), International Conference on Harmonization (ICH), and local regulations, or having a person with a power of attorney willing to provide written informed consent.

gCJD patients’ exclusion criteria:

Any other medical or psychiatric condition or laboratory abnormality, which in the investigator’s opinion might preclude participation.Previously obtained MRI scan with evidence of clinically significant neurological disorder other than CJD.Current anticoagulant treatment (e.g. Non-vitamin K Antagonist Oral Anticoagulants (NOACs), Warfarin, Low Molecular weight Heparin) that might preclude safe completion of LP.Conditions that preclude the safe performance of LP, such as severe lumbar spinal disease, bleeding diathesis, or clinically significant coagulopathy or thrombocytopenia.Conditions that preclude the safe performance of MRI scannings such as subjects who have a pacemaker, aneurysm clips, artificial heart valves, ear implants, metal fragments or foreign objects in the eyes, skin, or body, or any other known contra-indication for MRI.Active malignant disease.

Healthy relatives (HR) inclusion criteria:

First–degree relative of an E200K gCJD patient.Age 50 years or older at baseline.Willingness to undergo genetic testing.Ability to provide written informed consent under GCP, ICH, and local regulations.Willingness and ability to comply with scheduled visits, required study procedures, and laboratory tests.

Healthy relatives’ exclusion criteria include a clinical diagnosis of CJD. Otherwise, exclusion criteria are the same as those described for gCJD patients.

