### Sample size calculation and statistical analysis

With the objective of identifying biological markers for early detection of gCJD, we intend to conduct a comparative analysis of marker levels between gCJD patients and healthy individuals, as well as between healthy carriers and non-carriers. Based on the Israel National Registry for CJD, the annual incidence rate of CJD is 51 cases, although this is believed to be an underestimation. About two-thirds of the reported cases are familial cases, and of these cases, almost all are carriers of the E200K mutation. Given our conservative estimate that 50% of new cases of gCJD will be referred to our center, we anticipate that we will receive 15 new gCJD patients each year, for a total of 60 patients during the study period. Furthermore, we anticipate that approximately one-third of these patients, or 20 in total, will be willing to participate in the study.

With a conservative estimation of 3 first-degree HR per gCJD patient, this enables a population pool of > 100 per study period. As the E200K is an autosomal dominant mutation, 50% of the first-degree relatives of gCJD will carry the mutation. Based on Spudich et al. [34], the likelihood of developing gCJD is 0.45 in the age group of 51–60. According to Minikel et al., the average annual probability of onset (phenoconversion) for healthy carriers aged 40 to 80 years is 4.6% [35]. The primary aim of the study relates to biological markers for identifying phenoconversion. In our study, we referred to a positive CSF RT-QuIC.

CSF RT-QuIC has proven to be a relatively sensitive (73-97%) [13, 14] and a highly specific biomarker (99-100%) [12, 15–17] for diagnosing CJD, and it is now part of the standard diagnostic criteria [10]. Thus, considering a conservative estimate of a 13.6% phenoconversion rate among carriers (calculated as 3.4% expected conversion per year for 4 years) a sample size of 106 healthy relatives (53 carriers and 53 non-carriers) is required, based on a desired probability of type 1 error of 0.05 and a power of 80% (https://clincalc.com/stats/samplesize.aspx).

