#### Lumbar puncture (LP)

LP will be performed by an experienced neurologist at the Neurological Institute at TASMC. An LP for the collection of 15–20 ml of CSF will be carried out on all participants in the longitudinal study at baseline and at the end of every year thereafter, and when phenoconversion is suspected unless there is evidence of clinically significant coagulopathy or thrombocytopenia that would interfere with the safety of the procedure. LP will be performed with an a-traumatic needle (G25 pencil LP, AVMAD). Participants will be monitored during the procedure and following the procedure and will remain under bed rest supervision in the unit for 1.5 h following the procedure. They will be contacted by phone the day after the procedure as well as 7 to 10 days following an LP to monitor any adverse events.

The first 2ml of CSF will be processed to conduct standard analyses on cell count, protein, and glucose levels. The rest of the CSF will be centrifuged at 2000 g for 10 min at 24 °C and separated into 500ml aliquots in 1.5ml tubes, four of them with 0.03% CHAPS. The pellet will be suspended in 1.5ml of RNAlater Solution, placed at 4 °C for approximately 24 h, and stored at -80 °C.

Other fluid biomarkers in CSF will include T-tau, P-tau, NfL, Neurogranin, Neuronal glycolytic enzyme (NSE), GFAP, YKL-40 (also known as Chitinase 3-like 1), UCHL-1, S100B, PrP^sc^, and Mitochondrial malate dehydrogenase 1 (MDH1) levels.

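### The 106 relatives are sized on CSF RT-QuIC with no allowance for missing CSF, yet relatives may decline LP and are then tapped only on symptoms

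*Protocol article*

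**What the plan says.** **What the sample size rests on.** Under Sample size calculation and statistical analysis, the article says the primary aim concerns biological markers for identifying phenoconversion and adds: "In our study, we referred to a positive CSF RT-QuIC". The number is derived "considering a conservative estimate of a 13.6% phenoconversion rate among carriers", from 3.4% a year over 4 years. It gives 106 relatives, "53 carriers and 53 non-carriers", "based on a desired probability of type 1 error of 0.05 and a power of 80" per cent. No allowance for refused LP, dropout or missing CSF appears.

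**What is said about LP.** Three places bear on whether it is required:
- Lumbar puncture (LP): the procedure "will be carried out on all participants in the longitudinal study at baseline and at the end of every year thereafter", and also when phenoconversion is suspected. The only exception named is a clinically significant coagulation or platelet problem.
- Clinical neurological and cognitive evaluation: relatives unwilling to repeat the LP stay in the study, and "in the event that they exhibit symptoms suggestive of conversion into the disease, an LP is carried out as part of the clinical diagnostic process". The section then closes with the wider statement "Participants who do not wish to undergo LP are not excluded and are able to participate in the study".
- Study population, inclusion criteria for healthy relatives: "Willingness and ability to comply with scheduled visits, required study procedures, and laboratory tests".

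**The concern.** RT-QuIC as used here needs CSF, so a relative without an LP has no result on the marker that sized the study. Two things follow.

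**Ascertainment depends on the outcome.** A relative who accepts LP is tested yearly whether or not anything has changed. A relative who declines is tested during follow-up only if symptoms raise suspicion. Among decliners, results therefore come mainly from people who are converting. Presymptomatic positivity, the signal a study of preclinical markers is looking for, cannot be seen in them after they stop accepting LP. A positivity rate among those tested would over-represent converters.

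**The number enrolled is not the number with a result.** If 106 is the count needed with RT-QuIC known, each unreplaced refusal leaves the study short of its stated power. Only about seven events are expected in carriers, so a few unseen or differently classified results could alter the conclusion.

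**Working it through.** **Inputs.** From the article: carrier rate 0.136 over 4 years; 53 per group; type 1 error 0.05; power 80%. The article gives neither the non-carrier rate nor the sidedness. I take 0% and two-sided because together they reproduce 53. LP uptake is not given, so a range is assumed.

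**1. Reproducing 53 per group.** For a two-proportion test with pooled variance under the null:

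n = [z(0.975)·√(2·p̄·(1−p̄)) + z(0.80)·√(p1(1−p1) + p2(1−p2))]² / (p1−p2)²

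With p1 = 0.136, p2 = 0 and p̄ = 0.068:
- first term: 1.960 × √(2 × 0.068 × 0.932) = 1.960 × 0.3560 = 0.698
- second term: 0.8416 × √(0.136 × 0.864) = 0.8416 × 0.3428 = 0.2885
- n = (0.698 + 0.2885)² / 0.0185 = 52.6, rounded up to 53

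This matches the article. A one-sided test gives 42, a continuity correction 67, and a non-carrier rate of 1% gives 66. The 53 is therefore the uninflated number with a known outcome.

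**2. Power at smaller numbers with CSF (complete-case).** Power = Φ[(√n × 0.136 − 0.698) / 0.3428].

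| Assumed LP uptake | n per group | Power | Expected carrier events (n × 0.136) |
|---|---|---|---|
| 100% | 53 | 0.803 | 7.2 |
| 90% | 47 | 0.75 | 6.4 |
| 80% | 42 | 0.70 | 5.7 |
| 70% | 37 | 0.65 | 5.0 |

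Losing one person per group (n = 52) already gives 0.795.

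**3. Enrolment that would keep 106 with CSF.** N = 106 / uptake: 106/0.9 = 117.8, so 118; 106/0.8 = 132.5, so 133; 106/0.7 = 151.4, so 152. The article describes its pool of relatives only as more than 100.

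**4. Effect of symptom-triggered testing on the carrier rate.** Illustrative assumptions: a fraction d declines LP altogether, every converting decliner and no other decliner is tapped, and sensitivity is 1. The fraction tested is (1−d) + d × 0.136, and the apparent rate is 0.136 divided by that fraction.
- d = 20%: tested 0.8272 (about 44 of 53); apparent rate 0.136/0.8272 = 16.4%
- d = 30%: tested 0.7408 (about 39 of 53); apparent rate 18.4%
- d = 50%: tested 0.568 (about 30 of 53); apparent rate 23.9%

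**5. Why an analysis set should not require a later scheduled LP.** At 3.4% a year, carriers expected to convert in year 1 number 53 × 0.034 = 1.8, out of 53 × 0.136 = 7.2 over the study. Requiring a second scheduled LP would drop these early converters.

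**The case against.** Several counter-arguments have force.

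- **Many decliners will have some presymptomatic CSF.** The sentence that sets up the symptom-triggered LP concerns people unwilling to repeat the procedure, who have an earlier result. A reader might infer that every decliner is untested until onset. The text does not support that. Only the section's closing sentence reaches people who decline LP altogether.
- **Symptom-triggered LP is not peculiar to decliners.** The LP section provides it for everyone in the longitudinal study when conversion is suspected. Decliners differ in lacking scheduled LPs, and this is what creates the gap.
- **The article does not state a flawed analysis.** A reader might infer that scheduled and triggered results will be pooled, that untested relatives will be called negative, or that RT-QuIC sensitivity and its association with conversion will be inflated. None of these analyses is stated. Handling of missing CSF may well be in a fuller document.
- **The power loss assumes complete cases.** If triggered results from decliners count as events and everyone else stays in the denominator, expected carrier events remain near 7.2. That measures confirmed conversion, however, and leaves presymptomatic positivity in decliners unobserved.
- **The power figures are approximate.** With so few events the normal approximation is generous: Fisher's exact test gives 0.74 at 53 per group and 0.52 at 42. Much of the fragility comes from sparse events, not from LP refusal.
- **The inclusion criterion is a weak contradiction.** If LP is optional, it may simply not be one of the required procedures.

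What remains is the direct conflict between the LP section and the clinical evaluation section, the dependence of follow-up testing on symptoms among decliners, and a sample size with almost no margin.

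**Conclusion.** The concern holds within these limits. The article gives incompatible accounts of whether LP is done on all longitudinal participants, and its 106 is the number needed with RT-QuIC known. Power is 0.803 at 53 per group and falls below 80% with one loss per group. At assumed uptake of 90%, 80% and 70% it is about 0.75, 0.70 and 0.65, given a complete-case analysis, a 13.6% rate that applies to RT-QuIC positivity, 0% in non-carriers and a two-sided test. The rise from 13.6% to 16.4% at 20% refusal illustrates direction and scale under stated assumptions; it is not a forecast. The actual shortfall cannot be fixed from the document, because no uptake is given. The calculation behind 106 is not itself wrong, and the opt-out is not the fault. The fault is that the stated power ignores it.

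**What to change.** 1. Reconcile the LP section, the clinical evaluation section and the wording on required procedures in the inclusion criteria, so that they agree on whether LP is required. Nothing here calls for removing the opt-out.
2. State an assumed LP uptake and restate power for the number of relatives expected to have CSF.
3. Base the preclinical RT-QuIC analysis on relatives with at least a baseline scheduled LP. Censor at the last scheduled LP or at conversion and do not require a later LP, so that early converters are kept.
4. Report symptom-triggered LPs separately as diagnostic results, in all participants.
5. Do not count untested relatives as negative.
6. Compare LP takers with decliners on baseline data.

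The cost is wording in the protocol and analysis plan, a less favourable stated power, and fewer events in the preclinical analysis, because positives first found at a triggered LP move to the diagnostic report. No procedure is added.

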### Cognitive assessment

Standardized neuropsychological tests assessing different cognitive domains will provide an in-depth evaluation of cognitive function. These tests include the following:

Montreal Cognitive Assessment (MoCA) [37] - A 30-point cognitive screening instrument that assesses visuospatial, executive, naming, attention, language, abstraction, delayed recall, and orientation domains.Verbal Fluency tests [38] on which participants name as many different words that begin with a designated letter or as many items that belong to a given semantic category in one minute. The score is the sum of all correct words produced.The Motor-free Visual Perception Test (MVPT-3) [39], which measures the ability to discriminate dominant features of different objects, including the ability to discriminate position, shapes, and forms, and the ability to perceive the positions of objects in relation to oneself and other objects. This test also examines visual memory, the ability to distinguish an object from the surrounding objects, and the ability to perceive a whole figure from its fragments.The Frontal Assessment Battery (FAB) [40] targets executive functions, including attention span, working memory, motor planning, abstraction, and inhibition.Digit span (Wechsler Adult Intelligence Scale, Third Edition, WAIS-III) which measures verbal working memory by asking participants to repeat digits forward and backward.The Cookie theft picture description from the Boston Diagnostic Aphasia Examination–Third Edition (BDAE).Trail Making Test (TMT) parts A & B [41] which estimates visual search, speed of processing, and shifting attention.

### Affect, behavior, and habits

The following questionnaires assess the level of anxiety, depression, stress, and personality traits:

The Beck Depression Inventory (BDI) [42] which evaluates the presence and intensity of depression.The State-Trait Anxiety Inventory (STAI) [43] which measures emotional state anxiety, using 40 items.The Social Readjustment Rating Scale (SRRS) [44] aims to identify major stressful life events.The Big-5 Questionnaire [45] measures dimensions of personality through ratings of 44 items.

### Autonomic function

Questionnaires assessing autonomic function and sleep will be completed:

The Epworth Sleepiness Scale (ESS), a self-administered questionnaire collecting information on the propensity to fall asleep in eight different situations encountered commonly in daily life. Each situation is rated from 0 (no chance of dozing) to 3 (high probability of dozing), and the total score ranges from 0 to 24. Total scores of zero to 10 are normal, 10–12 are borderline, and scores from 12 to 24 are abnormal.The REM Sleep Behavior Disorder Screening Questionnaire (RBDSQ) is a 10-item self-rated questionnaire to assess sleep-wake disturbances. Sleep behavior disorder may represent early manifestations of progressive neurodegenerative disorders, including Parkinson’s disease. A score greater than 5 reflects RBD.SCOPA-AUT (Scales for Outcomes in Parkinson’s disease - Autonomic Dysfunction) - The SCOPA-AUT was developed to evaluate autonomic symptoms in patients with Parkinson’s disease as well as patients with Multiple System Atrophy. The scale is self-completed by patients and consists of 25 items assessing the following domains: gastrointestinal (7 items), urinary (6 items), cardiovascular (3 items), thermoregulatory (4 items), pupillomotor (1 item), and sexual (2 items for men and 2 items for women).

### Blood and urine samples

#### Samples handling and pre-processing

Participants will provide blood and urine samples when clinically assessed. They will be strongly encouraged to eat a low-lipid diet on the day of the test. Information on food intake will be collected. Samples will be delivered to the laboratory as soon as possible, and not more than 30 min after collection. Processing and extractions will occur immediately after the arrival of samples in the laboratory.

Serum extraction: To ensure serum clotting, the serum tube will be centrifuged at least 30 min after blood drawing (and no longer than 60 min) at 1500 g for 15 min at 4°c. Then, on ice, the supernatant will be transferred to a conical 15ml tube and then inverted gently. The supernatant will be evenly divided into four aliquots and frozen at -80°c.

Plasma extraction (K2EDTA tube): Tubes will be centrifuged for no longer than 30 min after blood drawing at 2000 g for 15 min at 25°c. The supernatant will be transferred to a conical 15ml tube and then inverted gently. Plasma will be divided into 8 aliquots of 0.5ml and frozen at -80°c. Buffy Coat (BC, K2EDTA tube): Immediately after transferring the plasma from the K2EDTA tube, BC will be cautiously collected to a labeled cryotube at RT and frozen at -80°c.

Urine processing: Urine tubes will be centrifuged upon arrival at 2500 g for 15 min at 4°c. Then, on ice, the supernatant will be transferred to a conical 15ml tube and then inverted gently. The urine will be divided between two conical 15ml tubes, 4ml to the first tube and the remainder to the second. If the total amount of urine is less than 5ml, the urine will be divided evenly between the tubes. The tubes will be frozen at -80°c.

Whole blood tubes will be frozen no longer than 60 min after the blood draw.

PAX tubes will be collected for future RNA extraction. The tubes will be kept at room temperature for 3–26 h and then frozen at -80°c. Whole blood for DNA extraction will be collected only at the first visit. The tube will be placed at 4°c until DNA is extracted.

Sample data will be inserted into a dedicated database software.

#### Genetic testing

Genomic DNA will be extracted from whole blood samples and will be genotyped for the PRNP-E200K mutation (rs28933385, TaqMan genotyping assay C_27531205_10_F_; Applied Biosystems, Foster City, CA, USA). Confirmation for the *PRNP* mutation will be done by a polymerase chain reaction and Sanger Sequencing. Confirmation by sequencing will be performed for healthy relatives that are shown to be E200K carriers and for all CJD patients.

#### Clinical laboratory tests

Blood will be collected for standard clinical laboratory tests: Complete Blood Count, Chemistry screen, Glycohemoglobin test, Vitamin D, Vitamin B12, Thyroid Function Tests, C-reactive protein, Lipid profile, International Normalized Ratio, Prothrombin Time, and Partial Thromboplastin Time.

Other fluid biomarkers in blood will include total-tau (T-tau), phosphorylated-tau (P-tau), Neurofilament light chain (NfL), Glial fibrillary acidic protein (GFAP), and Ubiquitin carboxy-terminal hydrolase L1 (UCHL-1).

